*Switching* refers to the ability to shift between tasks [68], and will be assessed by the Matching Task [70, 71]. In this task, four different geometric figures (a circle, a hexagon, a square, and a triangle), presented in the colors blue, green, red, or yellow are used as stimuli. The task consists of 31 task runs, each consisting of on average six trials (range: 4–8 trials). During a trial, a colored reference figure is displayed in the upper half of the screen, and four colored match figures are shown in the lower half of the screen. Participants will be instructed to match the reference figure to one of the match figures according to shape or color. Whether participants have to match according to shape or color, will be randomly chosen and indicated by a cue that is displayed for 1000 ms. Participants can push one of four buttons on the keyboard which corresponds to one of the four match figures in the lower half of the screen. During one single task run, participants have to match either according to color or shape. The color-shape combinations are shown in a way that there is one ‘right’ option. Half of all task runs consisted of ‘switch’ runs, in which the type of cue differs from the previous run. The other half consists of ‘repetition’ runs, in which the type of cue is identical to the previous run. The duration of the test is approximately six minutes. Both the mean reaction time for switch runs and repetition runs will be used as an outcome measure for switching (for more detailed information about this task, see [70]).

*Inhibition* addresses one’s capability to deliberately inhibit dominant and automatic responses to certain stressors [68]. Inhibition will be measured with the Sustained-Attention-to-Response Test (SART [72]). During this test, digits (ranging from 1–9) are displayed one-by-one in the centre of the screen. Participants are instructed to push a button on a button-box when a digit appears on the screen, except when the digit is a ‘3’, which occurs in 11.1 % of the cases. A total of 450 digits will be presented, each with a duration of 250 ms. The interval between digits is 850 ms. The number of inhibition errors (thus, when a participant presses the button when a ‘3’ appears on the screen), will be taken as a measure for inhibition.

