### Analyses of primary and secondary outcomes

We will use intention-to-treat analysis, meaning that all participants who are randomized to a condition will be included in the analyses. To test the efficacy of the exercise intervention (i.e. change in primary and secondary outcomes from pre [T0] to post [T6]), we will perform 2x2 repeated measures (M)ANOVAs with condition (exercise versus wait list) as between-subjects factor, and time (pre [T0] versus post [T6]) as within-subjects factor. We will conduct a RM-MANOVA for the three indicators of work-related fatigue together (*Hypothesis 1*). Furthermore, we will conduct separate RM-(M)ANOVAs for respectively self-efficacy (*Hypothesis 2a and 2b*), sleep (*Hypothesis 2c and 2d*), work ability (*Hypothesis 2e*), cognitive functioning (*Hypothesis 2f*), and aerobic fitness (*Hypothesis 2 g*). The Matching Task will be analyzed using a 2x2x2 mixed design ANOVA, with ‘run type’ (switch versus repetition), and time (pre versus post) as within-subjects factors, and condition as between-subjects factor (exercise versus wait list). In all analyses, we are particularly interested in the ‘condition x time’ interaction, because this indicates that the conditions differ from each other with respect to the development of the outcome measure over time. If applicable, significant interactions will be further examined by paired-sample t-tests. Partial eta-squared will be reported as effect size.

Additionally, to obtain more thorough insight into the clinical meaningfulness of the changes brought about by the exercise intervention [81], we will perform a Chi-Square Test to see if the number of participants who score below cut-off scores of fatigue after the intervention period (T6) differs between the intervention and the control condition (emotional exhaustion <2.2 on the UBOS; overall fatigue: <22 on the FAS).

To investigate whether intervention-effects last during the follow-up period, for each primary and secondary outcome measure, a repeated measures MANOVA will be performed to see whether it differs between pre (T0), post (T6), 6 weeks after the intervention period (T7), and 12 weeks after the intervention period (T8). If the overall time effect of MANOVA is significant, post hoc tests will be carried out to exactly determine between what time points the outcome had changed. As follow-up measures are only available for the intervention condition, the control condition will not be included in these analyses.

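### Switching is scored by reaction time alone and read from the condition × time term, so a speed-accuracy shift in one arm could be reported as better switching

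*Protocol article*

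**What the plan says.** The protocol article, under Cognitive functioning, describes the Matching Task as a four-choice task: "Participants can push one of four buttons on the keyboard which corresponds to one of the four match figures". Every trial has a correct answer: "The color-shape combinations are shown in a way that there is one ‘right’ option". On its length: "The task consists of 31 task runs, each consisting of on average six trials (range: 4–8 trials". The outcome is then fixed: "Both the mean reaction time for switch runs and repetition runs will be used as an outcome measure for switching". No accuracy or error score is named for this task, and the reader is sent to a cited source for further detail.

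The same section scores the other two performance tests by accuracy: the 2-Back by the number of correct responses, and the SART by the number of inhibition errors.

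Under Analyses of primary and secondary outcomes: "The Matching Task will be analyzed using a 2x2x2 mixed design ANOVA, with ‘run type’ (switch versus repetition" and time as within-subjects factors, and condition as the between-subjects factor. The section then says "In all analyses, we are particularly interested in the" condition × time interaction. It makes no exception for the Matching Task, and it does not mention the three-way term.

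**The concern.** Two stated choices combine.

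- **The score.** Reaction time on a task where errors are possible can be read as ability only if accuracy is known to have held. Only the speed half is defined as an outcome.
- **The term.** Switching ability shows in how much slower a person is on switch runs than on repetition runs. Condition × time averages over run type and so discards that contrast. It answers whether one arm became faster overall.

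Strengths and limitations acknowledges that the study is not blinded, and the control is a wait list. The arms could therefore differ at T6 in motivation, effort or haste. A shift in the balance of speed and accuracy in one arm would move condition × time. The result could be reported as improved executive functioning under Hypothesis 2f when switching itself was unchanged or worse. An arm that became more careful would be penalised in the same way. Even a genuine speed-up, equal in both run types and with no loss of accuracy, would be read as switching when it is not.

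**Working it through.** The plan gives no figure to reproduce on this point. I checked the task arithmetic, then what each model term measures, then how far guessing could move each term.

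**1. Task arithmetic (from the article).** 31 runs × 6 trials on average = 186 trials. Six minutes is 360 s, and 360/186 = 1.94 s per trial, or (360 − 31)/186 = 1.77 s after removing 31 one-second cues. Thirty runs have a predecessor, giving 15 switch and 15 repetition runs, about 90 trials each. Chance accuracy with four options is 25%. The description is internally consistent.

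**2. What each term measures.** Let S and R be a participant's mean reaction times on switch and repetition runs.

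- Condition × time compares the arms on the pre-to-post change in (S + R)/2.
- Run type × time × condition compares the arms on the pre-to-post change in S − R.

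If one arm becomes faster by δ on both run types, the first term moves by δ and the second by zero. The term singled out in the plan responds to general speed; the one that isolates switching does not.

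**3. Guessing illustration (all inputs assumed).** At T6 a share p of one arm's trials are fast guesses taking g seconds and 25% correct. The rest are genuine responses, 95% correct. Then:

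- accuracy = (1 − p) × 0.95 + p × 0.25
- fall in mean reaction time, all trials = p × [(S + R)/2 − g]
- fall in the switch cost, all trials = p × (S − R)

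Example with R = 1.0 s, S = 1.2 s, g = 0.6 s, p = 0.10:

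- accuracy = 0.855 + 0.025 = 0.88
- all-trial fall = 0.10 × (1.1 − 0.6) = 50 ms
- correct-trial mean = (0.855 × 1.1 + 0.025 × 0.6)/0.88 = 1.086 s, a fall of 14 ms
- switch cost falls by 0.10 × 200 = 20 ms

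Ranges for R of 1.0 to 1.4 s, switch cost 0.1 to 0.2 s and g of 0.4 to 0.6 s:

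| Share guessed | Accuracy | Fall, all trials | Fall, correct trials only | Fall in switch cost |
|---|---|---|---|---|
| 10% | 88% | 45 to 110 ms | 13 to 31 ms | 10 to 20 ms |
| 5% to 20% | 91.5% to 81% | 23 to 220 ms | 6 to 68 ms | 5 to 40 ms |

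At 10% guessing, restricting to correct trials removes roughly 70% of the artefact (for example 1 − 14/50 = 72%). The three-way term is much less exposed but not immune, because guessing also shrinks the switch cost. That is why the error rate is needed as well as a change of term.

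**4. What a 50 ms shift could do.** The planned 108 less 20% dropout is 86.4, so about 43 per arm. With an assumed SD of change of 100 to 150 ms, 50 ms is 50/150 = 0.33 to 50/100 = 0.50 SD. A two-sided 5% comparison would then be significant in about 33% to 63% of trials. Holding the fall at 500 ms per guessed trial, 5% guessing (25 ms) gives about 12% to 21%, and 15% guessing (75 ms) about 63% to 93%.

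**The case against.** The strongest reply is that the article is silent, not wrong. It never says that errors are ignored or that all trials enter the mean, and it defers detail: "for more detailed information about this task, see [70". A reader might infer from the reaction-time score that error trials are included. The documents do not support that inference. The source or a fuller plan may restrict to correct trials, and an article may leave that out. This part of the reply stands, so I make no finding on the exclusion of error trials.

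A reader might also infer that the plan cannot test switching. It can: run type is a factor in the planned ANOVA, so the three-way term is in the model, and particular interest in one term does not rule out another. What remains is that the article singles out condition × time for all analyses and leaves the informative term for this task unnamed.

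Third, there are partial safeguards. Motivation, fatigue, demands and effort are rated around the tests at T0 and T6, and the other two performance tests are accuracy-based. A generally careless arm would be expected to do worse on those, so Hypothesis 2f as a whole does not simply reward carelessness. This is fair, but the ratings are not linked to errors on this task, and the other tests do not correct the switching result.

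Finally, the magnitudes are hypothetical, and nothing in the documents shows that one arm is likely to guess more. That is correct.

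**Conclusion.** The point holds in a limited form. The stated outcome for switching is speed only, and the stated term of interest does not isolate switching. A speed-accuracy shift in one arm could therefore pass for better switching. This follows from the article's own description of the task and analysis and does not depend on how error trials are treated. In the illustration, a correct-trials rule shrinks the artefact without removing it.

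The size is unknown. The millisecond and percentage figures show that a material bias is possible under assumed reaction times, accuracy, SDs and one-sided guessing. They do not estimate its likelihood and should not be read as a forecast of a false-positive rate. The reach is small: one of four indicators of cognitive functioning, under one secondary hypothesis. Hypothesis 1, the primary outcome and the sample size are untouched.

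**What to change.** - **Analyses of primary and secondary outcomes:** for the Matching Task, name run type × time × condition as the test of switching, and report condition × time as a test of general response speed.
- **Cognitive functioning:** add the error rate for switch runs and for repetition runs as a companion outcome, analysed in the same 2x2x2 model. State whether the mean reaction times use correct trials only.
- **Interpretation:** claim better switching under Hypothesis 2f only if speed improves on the named term without more errors.

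The cost is analysis wording and one extra reported outcome, with no added visits or participants. It assumes that the task software logs which button was pressed; the article implies this is possible, since one option is right, but does not say so. The three-way contrast is also expected to be less precise than an overall mean. The documents give no variances from which to size that loss.

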To obtain more insight into cognitive functioning, we will additionally evaluate the *subjective costs* (fatigue, motivation, demands, and effort) associated with doing these tests [73, 74]. These *subjective costs* will be measured using single item measures, answered on a scale from 1 (*not at all*) to 10 (*very much*). Before doing the cognitive tests, participants will rate how motivated they are to do the tests. Fatigue will be measured prior to and after the tests. In addition, after each cognitive test, participants will be asked to score how demanding the test had been. After completing all the tests, participants indicate how much effort they spent when doing the tests.

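### The SART inhibition score uses only presses on the 50 no-go digits, so a between-arm shift toward withholding could be read as an exercise effect on inhibition

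*Protocol article*

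**What the plan says.** Under Cognitive functioning, the protocol article describes inhibition as the capacity to hold back a dominant, automatic response and measures it with the SART. The instruction is "Participants are instructed to push a button on a button-box when a digit appears on the screen", with the digit 3 as the exception, "which occurs in 11.1 % of the cases". On length and pace: "A total of 450 digits will be presented, each with a duration of 250 ms", and "The interval between digits is 850 ms".

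The score is then fixed as the count of presses on the digit 3; the sentence that sets it ends "appears on the screen), will be taken as a measure for inhibition". No other SART quantity is named. For the Matching Task, in the same section, mean reaction time is the stated outcome.

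The section also collects single-item ratings of motivation, fatigue, demand and effort around the tests, for example "After completing all the tests, participants indicate how much effort they spent when doing the tests". Table 1 schedules these at T0 and T6. They do not enter the SART score.

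Under Analyses of primary and secondary outcomes, "we will conduct separate RM-(M)ANOVAs for respectively self-efficacy" and the other secondary outcomes, cognitive functioning among them. The condition x time interaction is the term of interest. Nothing from the go digits of the SART is brought into that analysis.

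**The concern.** A low count of presses on 3 shows successful withholding only if the participant was otherwise pressing as instructed. The go digits carry that evidence, and the score leaves them out. A participant who presses less readily on all digits will press on 3 less often, and the rule records this as better inhibition. Slower responding also carries no cost in the score, and it plausibly gives more time to recognise a 3.

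Participants know their condition, and the comparator is a wait list. The Strengths and limitations section plays down the lack of blinding on the ground that outcome assessors make no subjective judgement. That argument does not reach the participant's own response style on a speeded test. If caution or engagement changes differently between the arms from T0 to T6, the interaction for Hypothesis 2f would absorb the difference, in either direction.

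**Working it through.** **Trial counts (from the article).** With nine digits and one no-go digit, 450/9 = 50 no-go digits and 450 - 50 = 400 go digits. The stated share is reproduced: 50/450 = 11.1%.

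**The rule applied to fixed response patterns.** Errors = 50 x P(press on 3); go omissions = 400 x (1 - P(press on go)).

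| Pattern | Errors | Go omissions |
|---|---|---|
| Press on every digit | 50 | 0 |
| Press at random on 50% | 25 | 200 |
| Press at random on 20% | 10 | 320 |
| Never press | 0 | 400 |

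None of these patterns distinguishes a 3 from any other digit, yet the score runs from worst to best as pressing declines. The last row is a limiting case that shows only the direction.

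**Modest shifts (assumed rates).** Use an equal-variance signal detection model with discrimination held fixed: d' = z(go press rate) - z(no-go press rate), so the no-go press rate = Phi(z(go press rate) - d'). The article gives no press rates, so two assumed starting points are shown.

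- Start at 98% go, 40% no-go: d' = 2.054 + 0.253 = 2.307.
- Start at 98% go, 30% no-go: d' = 2.054 + 0.524 = 2.578.

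| Go press rate | Go omissions | Errors, start 98/40 | Errors, start 98/30 |
|---|---|---|---|
| 98% | 8 | 20.0 | 15.0 |
| 97% | 12 | 16.7 | 12.1 |
| 95% | 20 | 12.7 | 8.8 |
| 93% | 28 | 10.1 | 6.8 |

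Worked entry: at 95% from 98/40, Phi(1.645 - 2.307) = Phi(-0.662) = 0.254, and 50 x 0.254 = 12.7. Twelve more omissions among 400 go digits (8 to 20) lower the errors by 7.3/20 = 37% in one case and 6.2/15 = 41% in the other. Discrimination is unchanged throughout.

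**From a participant to the trial contrast.** The interaction compares changes between arms, so only a differential shift matters. Suppose every participant starts at 98/40.

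- Neither arm shifts: (20 - 20) - (20 - 20) = 0.
- Both arms shift to 97%: (16.7 - 20) - (16.7 - 20) = 0.
- Only one arm shifts to 97%: (16.7 - 20) - (20 - 20) = -3.3 errors, with no change in discrimination.

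The model has no reaction-time term, so it shows the effect of withholding and not of slowing.

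**The case against.** The article contradicts nothing here. With eight of nine digits requiring a press, pressing is the dominant response, and a press on 3 is a direct failure to withhold it. The tests are described as validated, and the source cited for the SART cannot be checked here, so no departure from its scoring can be claimed. This stands as a reason to keep the error count.

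The article calls the count a measure of inhibition, which does not forbid reporting others, and descriptive go-trial data could be left to an analysis plan. That is fair for descriptive reporting. The scoring rule, however, was not left open: it is stated, and it decides how Hypothesis 2f will be read.

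Stable individual styles cancel in the condition x time term. No differential shift is demonstrated, and inattention could as well raise errors where pressing is automatic. All of this stands. The motivation and effort ratings at T0 and T6 also allow an arm difference in engagement to be noticed, though they do not correct the score.

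A reader might infer that the plan will in practice give a non-responder the best score. Participants are instructed to press and are tested at individual lab appointments, so nothing in the article suggests this would happen. A reader might also infer that slowing is shown to lower errors. The article shows only that speed is not scored; the benefit of slowing is inferred from the task, and the fixed pace limits it.

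Finally, adjusting for go reaction time at T6 would condition on something exercise may itself change, and a discrimination index arguably measures a different construct. Both points stand, and neither measure should replace the main score.

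**Conclusion.** The concern holds in a limited form. Because the go digits are ignored, a shift toward withholding that differs between arms from T0 to T6 could be read as an effect of exercise on inhibition. The same is plausible for slowing. The direction of the effect of withholding on the score follows from the rule itself. The sizes, such as 20 to 12.7 errors when go presses fall from 98% to 95%, rest on assumed press rates and an equal-variance model, and are illustrative only.

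The article does not support a stronger reading, namely that the inhibition result will be biased, that any bias would favour exercise, or that the error count is invalid. What is affected is one of four indicators of cognitive functioning, itself one of five secondary outcomes. The primary outcome and the sample size are untouched. The change is still worth making before the data are seen, because the article's scoring rule and stated analysis leave a response-style explanation of the inhibition result unchecked.

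**What to change.** Keep the count of presses on 3 as the inhibition score, and add to the analysis section:

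1. The number of go omissions and the mean go reaction time, from the same 450 trials, will each be analysed with the same 2x2 condition x time model and reported by arm beside the error count.
2. Fewer errors in an arm will be interpreted as better inhibition only if go omissions and go reaction time do not worsen in that arm relative to the other. This should be judged on the estimated differences and their confidence intervals, since a non-significant test alone does not show that nothing worsened. Otherwise the result will be described as compatible with a change in response style.
3. A go/no-go discrimination index may be given as a sensitivity analysis.
4. Adjustment for go reaction time measured after randomisation will not be the main analysis, because exercise may change it.

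No new testing is needed, assuming the test software keeps the response and its time for every digit. The cost is two extra secondary summaries and a more cautious conclusion on Hypothesis 2f.

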#### Aerobic fitness

We will measure aerobic fitness using the estimated maximal oxygen uptake (VO_2max_), obtained from the UKK walk test [75]. This test has found to be valid and feasible for a healthy adult population [75]. During this test, participants have to walk 2 km as fast as possible. The test will take place on a 400 m outdoor track in groups of (maximum) ten participants. Participants start individually every 30s. The instruction is as follows: “Walk the distance as fast as you can, but do not risk your health”. Immediately after the walk, the heart rate and walking time will be measured. The variables used to calculate VO_2max_ are walking time, heart rate, body weight, height, and gender (see [75] for exact equations).

We will also measure participants’ *subjective costs* of doing the UKK walk test. The questions used for this purpose are similar to those asked before and after the cognitive tasks, except that we add another question about how ‘short of breath’ participants are immediately after the test. Completion of the test, including filling out the items about subjective costs, takes about 25 min.

### Weekly measures during the intervention period

During the six weeks of the intervention period, each Wednesday all participants (intervention and control condition) will be requested to complete a short questionnaire that will be sent by email. Completion of the weekly measures takes five minutes.

#### Employee well-being

We will use twelve single-item measures as indicators of employees’ *weekly well-being* in order to obtain a detailed account of the course of these indicators during the intervention period. Single item measures are chosen because such measures require minimum effort to complete, and because they have been found to be valid indicators of employee well-being [76]. The items are introduced as follows: “Can you indicate with a report mark between 1 (not at all applicable) to 10 (extremely applicable) to what extent the following state of minds were applicable to you during the previous two days?” The items are: “healthy”, “tired”, “tense”, “happy”, “satisfied”, “energetic”, “stressed”, “vital”, and “irritated”. The response scale from 1 to 10 is based on the typical Dutch grade notation system.

Additionally, three single item measures to assess participants’ *weekly self-efficacy* regarding exercise, work, and other private personal goals will be as follows: “Can you indicate with a report mark between 1 (not at all certain) to 10 (extremely certain) how certain you are that you can reach your goals regarding “exercise”, “work”, “other private personal goals” during the previous two days?

Furthermore, to measure employees’ *weekly sleep quality*, the 6-item sleep quality scale derived from the Dutch Questionnaire on the Experience and Evaluation of work will be used [63]. As these items were originally developed for chronic sleep complaints, the scale is adapted for weekly measurement. An example item is: ‘I slept well last week’ (reversed; 1 = *yes*, 0 = *no*). Next to sleep quality, also the mean hours sleep a night will be assessed (i.e. ‘*sleep quantity’*).

